#### Secondary parameters related to efficacy:

1. Association between specific composition of gut microbiome and the severity of the side effects (hi squared value, p-value);
2. The association between DNA methylation at specific loci, gene expression profile with severity of side effects (hi squared value, p-value);
3. The association of the composition of gut microbiome with altered DNA methylation or transcriptome profiles (hi squared value, p-value).
4. Association between pharmacokinetic parameters and specific taxonomic units, changes in DNA methylation profiles and transcriptome profiles (p-value).

The metagenome analysis will provide information on the effect of metformin on the microbial gut, its functions, and the role of microbial in metformin tolerance. The microbiological analysis will be carried out in the specimens of the feces using the methods described above. The effect of metformin on the intestinal microbial will be evidenced by the altered microbial composition and function - a statistically significant change in the number of taxonomic units, genes, proportions, identified metabolites and their concentrations.

Metagenomic analysis will provide information about the metformin-induced alterations in gut microbiome and its role in the tolerance of metformin. The metagenomic analysis will be performed by using stool samples and the effect of metformin will be evaluated by altered composition and function of gut microbiome - significantly changed number of taxonomic units, genes, proportions, metabolites and their concentrations.

Venous blood samples will be further used for DNA methylation and RNA expression analysis. The effect of metformin on the epigenetic regulation will be confirmed by statistically significant alterations in the DNA methylation and transcriptome profiles after the administration of metformin, and the functionality of these alterations will be confirmed based

on the correlation between the DNA methylation profiles and the RNA expression intensity at specific loci.

The ability of metformin to induce alterations in the composition of gut microbiome and epigenetic gene regulation will be analyzed using biological materials (venous blood and feces) derived from three treatment-related time points: before metformin use, 10 hours after the first dose of metformin and 7 days after metformin use. For each participant of the study, alterations in the diversity and proportion of microbial taxonomic units of the gut microbiome and metabolite composition and concentrations in stool samples will be determined. In addition, metformin-induced alterations in DNA methylation and transcriptome profiles will be analyzed. Data obtained from biological samples collected before the use of metformin will be considered as a reference. By combining the results of all participants, conclusions will be drawn on the effect of metformin on the composition of gut microbiome and epigenetic regulation. Statistical data analysis will allow to determine an association between microbial composition and severity of adverse reactions, microbial composition and changes in DNA methylation or RNA expression profiles, DNA methylation profiles and drug tolerance.

### **Endpoints of the study**

The primary endpoint of the study is a significant change in the composition of the gut microbiome in healthy subjects (composition and proportion of taxonomic units) after administration of metformin.

Secondary endpoints of the study:

- 1) Significant alterations in DNA methylation profiles and RNA expression levels in healthy subjects following metformin use;
- 2) Association of DNA methylation profiles with severity of adverse reactions.
- 3) Association of specific gut microbial taxonomic units with severity of adverse reactions;
- 4) The association of specific taxonomic units with changes in the metabolite profile in the blood / faeces.
- 5) Association of pharmacokinetic parameters with specific taxonomic units of gut microbiome and changes in DNA methylation and gene expression profiles.

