### **Secondary objectives:**

- 1) Evaluate gut microbiome taxonomic profile in association of metformin tolerance;
- 2) Distinguish the changes in gut microbiome induced by metformin administration from those initiated by diet;
- 3) Evaluate changes in white blood cell RNA expression and DNA methylation profiles;
- 4) Analyze the association between metabolite profile changes in blood/faeces and the gut microbiome composition;
- 5) Determine the effect of metformin pharmacokinetics on gut microbiome composition and DNA methylation profiles.

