***3rd visit - Study Day 4.*** Blood samples (7 - 13 ml) will be collected from the participant's at fasting-state for further genotyping, DNA methylation, RNA expression and metabolite analysis. Participants will deliver a filled general questionnaire previously collected stool samples. The investigator will provide each participant with 14 film-coated *Metforal* 850 mg tablets and re-instruct on the mode of administration, duration, dose, storage and return of the drug. The administration of *Metforal* 850 mg will begin.

**4th visit - Study Day 4.** 10 hours after the first dose of the *Metformal* 850 mg (before the second dose), blood samples (7 - 13 ml) from the study participant will be repeatedly collected for DNA methylation, RNA expression and metabolite analysis. Participants will be instructed to collect the second stool sample on day 5 of the study.

**5th visit - Study Day 6.** Participants will be asked to attend a control visit in order to obtain the information about the participant's well-being and evaluate their compliance with the study protocol. Participants will bring the stool samples collected on Day 5.

**6th visit - Study Day 11** (the day after the last intake of *Metformal* 850mg). Blood samples at fasting-state will be obtained for DNA methylation, RNA expression and metabolite analysis. If necessary, the participant will return the unused *Metformal* 850 mg tablets. Participants will be asked to collect a stool sample within this day.

**7th visit - Study Day 12,** The final inspection visit. Participants will bring the stool samples collected on Day 11, filled diet diaries and questionnaire on side effects. The participant of the study will be informed about the upcoming telephone call on the 13th day of the study.

**Phone call visit - Study Day 13.** The investigator will contact each participant by phone, making sure about the participant's well-being and any side effects observed. If necessary consultation of physician or other certified specialist will be recommended. The investigator will answer any question regarding the progress of the study and inform the participants about the end of the active participation in the study.

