### **Dosage, packaging, storage of the investigational drug**

Each study participant will take 850 mg of metformin twice a day (10 to 12-hour interval) for a week. During the study, the therapeutic daily dose of the drug (1700 - 2250 mg) will not be exceeded. Participants will use the medication during or after eating with a glass of water to reduce the risk of side effects. Each study participant will receive a package of 14 *Metforal* 850 mg tablets during their 3rd visit. Participants will be instructed on the dosage, regimen, duration and possible side effects of the medication. According to the manufacturer's instructions, the product does not require any special storage conditions. The drug will be delivered to the research participant in its original package - PVC / Aluminum plate.

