### **Blood sample collection**

Within the framework of the study, venous blood samples (7 - 13ml) will be collected from participants (1) during the verification period, (2) immediately before the use of metformin, (3) 10 hours after the first dose of metformin, (4) 7 days since the beginning of metformin administration. During the verification period, the participant will donate a blood sample in any E. Gulbis laboratory (11 ml) for hematological and biochemical analysis. Blood samples for the analysis of DNA, RNA and metabolites will be collected on day 4 of the study (before and after the first dose of metformin) and on day 11 at LBMC. Venipuncture will be performed by a certified medical practitioner using appropriate equipment.

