### **Methodology for data statistical analysis**

Most of the data within the study will be obtained by massive parallel sequencing techniques, therefore, data pre-processing and specific preparation for statistical analysis is needed (e.g., removing low quality data or data that do not correspond to statistical standards). Data analysis will be performed using such softwares as mothur v.1.39.1, R, RStudio, Galaxy and others. The applied methodology for data statistical analysis may be changed according to offered possibilities, and within the study, the used approaches will be updated to ensure usage of the most recent, best quality, and suitable software, tools, tests, and their versions.

For the gut microbiome data, the sample inner (alpha) diversity and significance of its changes will be calculated (by Shannon index, t-test), as well as performed evaluation of inter-

sample (beta) diversity (principal coordinate analysis (PCoA, R, “vegan”). The statistically significant changes within every taxonomic level will be calculated (statistical tests: t-test, F-test, GLM, regression analysis; R „metagenomeSeq”, „edgeR”, „limma”, „lme4”, „lmerTest”, „multcomp”, „rgl”, etc.).

The data on methylation and RNA expression profiles will be used to determine genomic regions and their associated pathways with significantly altered DNA methylation or RNA expression levels (statistical tests: t-test, F-test, GLM, regression analysis; R „edgeR”, „DESeq2”, „asmn”, „sva”, „limma”, „lumi”, „wateRmelon”, „TCGAMethylation450k”, etc.).

Biochemical, haematological, and anthropometric characteristics will be used as covariates in the performed statistical analyses.

After collection of all data, the following associations will be assessed:

- Between abundance of specific taxonomic groups and severity of observed side effects (chi-squared test);
- Between changes in DNA methylation profile and severity of observed side effects (ANOVA);
- Between abundance of specific taxonomic units and changes in DNA methylation profile (ANOVA);
- Between pharmacokinetic characteristics and abundance of specific taxonomic groups, changes in DNA methylation profile (ANOVA).

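### Secondary objective 5 and endpoint 5 speak of metformin pharmacokinetics, but the blood schedule yields only two post-dose concentrations, one of them at no fixed time after dose

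*Protocol*

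**What the plan says.** Four places in the protocol rest on metformin pharmacokinetics, and none names a parameter:

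- Secondary objective 5: "Determine the effect of metformin pharmacokinetics on gut microbiome composition and DNA methylation profiles".
- Secondary parameters related to efficacy, item 4, which uses the term pharmacokinetic parameters.
- Endpoints of the study, secondary endpoint 5: "Association of pharmacokinetic parameters with specific taxonomic units of gut microbiome and changes in DNA methylation and gene expression profiles".
- Methodology for data statistical analysis, last listed association: "Between pharmacokinetic characteristics and abundance of specific taxonomic groups, changes in DNA methylation profile (ANOVA").

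Blood sample collection sets the post-dose draws at "3) 10 hours after the first dose of metformin, (4) 7 days since the beginning of metformin administration". It says that samples for DNA, RNA and metabolite work are "collected on day 4 of the study (before and after the first dose of metformin) and on day 11 at LBMC". The visit list under Observational period places the 10 h draw before the second dose. It describes the Day 11 draw as fasting and "the day after the last intake of" the study drug, without an hour. On dosing, the protocol says "Each study participant will take 850 mg of metformin twice a day (10 to 12-hour interval) for a week", and the section on administration says that intake is not directly supervised.

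The only drug measure described is concentration. DNA and RNA analysis uses the plasma level as an additional factor in the methylation analysis. Stool sample analysis provides for measuring metformin in both blood and stool.

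**The concern.** The phrase pharmacokinetic parameters usually means quantities such as peak, area under the curve, half-life and clearance. One late sample after the first dose and one after the fourteenth, with nothing earlier than 10 h after the first dose, do not support these for an individual. The protocol describes no serial profile, no urine collection and no population model. The schedule is fixed here, so a statistical analysis plan could define terms but could not add samples.

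A second issue concerns Day 11 only. A level taken at an uncontrolled time after an unsupervised dose mixes drug handling with sampling time. If the report presents associations with that level as evidence about pharmacokinetics, the label claims too much, and the associations themselves are weakened.

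**Working it through.** The plan states no figure on this point, so there is none to reproduce. The check has three steps.

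**1. Count the samples.** There are three research draws per participant: Day 4 before the drug, Day 4 at 10 h, and Day 11. Two are post-dose, each from a different dosing state (after 1 dose and after 14).

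**2. Are parameters identifiable?** The simplest oral model, with one compartment, is C(t) = D·ka / [V(ka − k)] · (e^(−kt) − e^(−ka·t)), with k = CL/V. It has three unknowns (ka, CL/F, V/F) against two concentrations.

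Illustration with assumed reference values that are not in the documents: ka 0.5 per h, CL/F 60 L/h, V/F 400 L, D = 850 mg, and 14 doses 12 h apart.

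- k = 60/400 = 0.15 per h.
- C(10 h) = 850 × 0.5 / (400 × 0.35) × (e^(−1.5) − e^(−5)) = 3.036 × (0.2231 − 0.0067) = 0.657 mg/L.
- Summing all 14 doses, the level 12 h after the last dose is 0.594 mg/L.

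Holding these two concentrations fixed and solving for CL/F and V/F at other absorption rates gives an exact match each time:

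| ka (per h) | Single-dose AUC (mg·h/L) | Cmax (mg/L) | Tmax (h) | Half-life (h) |
|---|---|---|---|---|
| 0.25 | 12.3 | 0.99 | 4.5 | 3.6 |
| 0.5 | 14.2 | 1.27 | 3.4 | 4.6 |
| 1 | 16.6 | 1.74 | 2.3 | 4.75 |
| 3 | 18.4 | 2.30 | 1.1 | 4.75 |

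The same two measurements fit a 2.3-fold range of peak (2.30/0.99) and a 1.5-fold range of area (18.4/12.3). Even if ka were known exactly, 10% error in each concentration gives a simulated 95% range for area of 11.7 to 19.9 around the true 14.2. With 20% error the range is 10.4 to 38.3.

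**3. How much does Day 11 timing matter?** In the same illustration, drawing 10, 12 or 14 h after the last dose gives 0.79, 0.59 or 0.44 mg/L for one person.

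For correlations, take late log-linear decline and timing error unrelated to the other variables. The timing variance on the log scale is (s_t · ln2 / half-life)². Reliability is s_b² / (s_b² + timing variance), and a true correlation is multiplied by its square root. Assumed values, none in the documents: s_t = 1.5 h, half-life 3 to 7 h, s_b (between-person SD of log concentration) 0.3 to 0.5.

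- Half-life 3 h: timing variance = (1.5 × 0.693/3)² = 0.120. With s_b = 0.3, reliability is 0.09/0.210 = 0.43, factor 0.65. With s_b = 0.5, it is 0.25/0.370 = 0.68, factor 0.82.
- Half-life 7 h: timing variance = (1.5 × 0.693/7)² = 0.022. With s_b = 0.3, reliability is 0.09/0.112 = 0.80, factor 0.90. With s_b = 0.5, it is 0.25/0.272 = 0.92, factor 0.96.

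The factor therefore runs from 0.65 to 0.96.

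**The case against.** The protocol never says that it will estimate a peak, area, half-life or clearance. The one drug measure it describes is concentration, and associations with concentration can be analysed. Which measure is meant could be defined in a statistical analysis plan. This stands. A reader might infer that the trial cannot address objective 5 at all; the documents do not support that. They support only that the wording is broader than the measurement.

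Stool metformin is also measured. The protocol's background puts the drug level in the small intestine at about 30 to 300 times that in plasma, so the stool level is a relevant exposure for the gut taxa half of endpoint 5. This stands, and any rewording must keep the stool measure.

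A reader might extend the timing problem to both plasma samples. The 10 h draw is tied to the first dose and precedes the second, so the argument applies to Day 11 only.

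A reader might also infer from the mention of ANOVA that concentration will be cut into groups. The same section lists GLM and regression, and nothing says that levels will be grouped.

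Whether time since dose will be used in the analysis may be settled in documents not shown. The table of anticipated problems has skipped tablets noted in the diet diary and deviations considered in data processing. However, the protocol nowhere asks for dose clock times, and no later adjustment is possible unless they are recorded.

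Finally, the size rests on outside assumptions and ranges from material to trivial.

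**Conclusion.** The point holds as a mismatch between wording and measurement. Two post-dose draws give two plasma concentrations, and individual pharmacokinetic parameters in the usual sense cannot be derived from them. That conclusion depends only on the schedule (two data points, at least three unknowns); the numerical ranges in the illustration depend on the assumed reference values. A population model with outside information could give shrunken individual estimates, but the protocol describes none.

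The Day 11 plasma level also carries variation from time since dose. Under the stated assumptions this multiplies true correlations by 0.65 to 0.96. The 10 h level is not affected in this way.

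Severity is low. This is the last of five secondary endpoints in a study that calls itself exploratory, and the primary endpoint is untouched.

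**What to change.** - In secondary objective 5, secondary parameter 4, secondary endpoint 5 and the last listed association, replace the pharmacokinetic terms with metformin concentration in plasma (10 h after the first dose, and on Day 11) and in stool at the scheduled post-dose collections.
- Record the clock times of the last dose and of the Day 11 blood draw.
- Adjust the log Day 11 plasma concentration for hours since the last dose.

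The cost is a protocol wording change, two clock times per participant and a more modest objective. No extra samples and no change to dosing are needed.

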### **SAFETY CONSIDERATIONS**

The research safety assessment will be carried out during each visit based on the information provided by participant on their well-being and health status since the beginning of *Metforal* 850 mg administration or previous visits. All participants of the study will be advised to inform the research organizers by telephone on any arisen health risks also outside the time of visits, if necessary. During the study all the side effects observed will be documented in detail in a specific questionnaire, indicating the type of side effects observed, time, and frequency of recurrence. Approximately 72 hours after the last dose of *Metforal* 850 mg the investigator will survey on phone all participants involved in the study in order to obtain more

information and evaluate their state of health and, if necessary, recommend visiting physician or certified specialist.

If any of the study participants is harmed as a result of the clinical trial, the compensation will be paid in accordance with the sponsor's concluded insurance contract. Visits to the physician, in case of side effects or adverse events will be compensated after the submission of payment document and a physician's conclusion that the cause of observed side effects is metformin therapy.

### **Definitions**

***Adverse Event (AE) or Adverse Experience*** - any unfavourable and unintended sign (including an abnormal laboratory finding), symptom, or disease temporally associated with the use of a medicinal product, whether or not considered related to the medicinal product.

***Serious Adverse Event (SAE) or Adverse Drug Reaction*** - any adverse drug event (experience) occurring at any dose that in the opinion of either the investigator or sponsor results in any of the following outcomes: 1) Death 2) Life-threatening adverse drug experience 3) Inpatient hospitalization or prolongation of existing hospitalization (for > 24 hours) 4) Persistent or significant incapacity or substantial disruption of the ability to conduct normal life functions 5) Congenital anomaly/birth defect 6) Important Medical Event (IME) that may not result in death, be life threatening, or require hospitalization may be considered a serious adverse drug experience when, based upon medical judgment, it may jeopardize the patient or subject and may require medical or surgical intervention to prevent one of the outcomes listed in this definition.

### **AE classification by severity:**

***Mild*** - Awareness of signs or symptoms, but easily tolerated and are of minor irritant type causing no loss of time from normal activities. Symptoms do not require therapy or a medical evaluation; signs and symptoms are transient.

***Moderate*** - Events that introduce a low level of inconvenience or concern to the participant and may interfere with daily activities, but are usually improved by simple therapeutic measures; moderate experiences may cause some interference with functioning

***Severe*** - Events that interrupt the participant's normal daily activities and generally require systemic drug therapy or other treatment; they are usually incapacitating

### **Assessment and reporting of adverse reactions**

The adverse reactions observed will be documented by the participant at the end of the active period of the study by using a specific questionnaire on side effects. The investigator will immediately inform the sponsor of any serious adverse event related to the subjects involved in the clinical trial. The sponsor will ensure that all undesirable events reported by the investigator or his research team are documented. At the end of the active period of the study the investigator does not apply monitoring of undesirable events to subjects involved in the clinical trial. If the

investigator receives information about serious adverse events after the trial is completed, the investigator will report it to the sponsor.

### **Potential benefits and risk factors for the study participants**

Participation in the study is not directly related to personal benefits of participants. Participation in the study, blood tests, genomic and microbial analysis conducted within the framework of the study are free of charge, and participants will receive the results of hematological and biochemical blood tests.

The risk factors for the participation in the study are related to the potential side effects of *Metforal* 850 mg. Based on the Summary of Product Characteristics gastrointestinal side effects are the most common (more than 1 in 10 people) in adults: indigestion, nausea, vomiting and diarrhea, abdominal pain, loss of appetite. Common (affects less than 1 in 10 people) alterations in taste, very rare (affects less than 1 in 10,000 people) skin reactions (erythema, itching and urticaria), abnormal liver function tests, hepatitis, decreased vitamin B12 blood. Very rare but serious side effect is metformin-induced lactic acidosis. Venipuncture will be performed by certified medical staff. In rare cases, a small amount of blood flushing may occur, or, less rarely, a slight localized inflammation of the skin. Collection of the stool samples does not endanger the health of the participant if general hygiene requirements are met.

In order to minimize the risk of undesirable effects, inclusion / exclusion criteria were thoroughly developed taking into account the contraindications for metformin listed in the Summary of Product Characteristics. Study participants who have moderate or severe side effects will immediately stop the use of the medication and, if necessary, will be advised to consult a physician or certified specialist. Participants will be asked to inform the investigator about the side effects observed, by documenting their observations in questionnaire on side effects at the end of the study. Participants will be informed about the risks of the study prior to the study, emphasizing their rights to discontinue the participation at any time and to inform that refusal to attend or withdrawal from the study will not result in any sanctions against them. The participant will confirm his awareness of the potential risks of the study by signing the informed consent form.

